### ****GLOSSARY of Terms and Abbreviations****

AE Adverse Event

CI Chief Investigator

CRF Case Report Form

ICF Informed Consent Form

IPAQ International Physical Activity Questionnaire
JRMO Joint Research Management Office

Participant An individual who takes part in a clinical trial

PIS Participant Information Sheet

R&D Research and Development

RCT Randomised Controlled Trial

REC Research Ethics Committee

TSC Trial Steering Committee

### SUMMARY/SYNOPSIS

| **Short Title** | 5-2 Study |
| --- | --- |
| **Methodology** | Randomised controlled trial |
| **Study Centre** | Health and Lifestyle Research Unit, [name] |
| **Objectives/Aims** | 1. Determine the effectiveness of the 5-2 diet combined with multi-session group support compared to the 5-2 diet delivered in a self-help format and to standard advice on diet and physical activity, in terms of weight loss at 6 weeks, 3 months (self-reported), 6 and 12 months 2. Explore predictors of, and barriers and facilitators to, adherence to the 5-2 diet. |
| **Number of Participants** | 300 |
| **Main Inclusion Criteria** | Adults, aged 18 years and older, with a BMI ≥30kg/m2, or BMI≥28kg/m2 with comorbidities |
| **Statistical Methodology and Analysis (if applicable)** | The primary analysis will compare weight loss between the three groups at 6 months, adjusting for baseline weight. We propose to implement a strict intention to treat (ITT) analysis as our primary outcome, with participants lost to follow-up included as achieving no weight loss. |
| **Study Duration** | 30 months |

### INTRODUCTION

Over a quarter of adults in England are obese [1], with obesity more prevalent in disadvantaged socioeconomic groups [2, 3]. Obesity is associated with a number of adverse health conditions including cardiovascular disease, type 2 diabetes, osteoarthritis and a number of cancers. Weight loss has been shown to improve many of these illnesses, and to reduce all-cause mortality [4, 5], with a maintained weight loss of 5% being sufficient to produce clinically significant benefits [6].

Treatments for obesity are an important focus across health research, policy, and commissioning arenas. Frontline health professionals are expected to assist people with weight problems by recommending healthy eating and physical activity, complemented as needed by drug therapy and a referral to a local weight management service. Local weight management services now come under the remit of public health departments at local councils. Public health commissioners typically contract non-NHS providers of varied quality. The services typically offer advice on food and physical activity combined with varied types of behavioural support. As with other services that provide face-to-face lifestyle interventions, only a small minority of the target group accesses them. The results in terms of throughput and weight loss are not generally monitored and so remain largely unknown.

Substantial resources are now being invested in such services and there is an urgent need to identify approaches with the best reach and with at least some evidence base.

**Intermittent Fasting and the 5-2 diet**

A novel type of intermittent energy restriction (IER) was introduced in the UK by a BBC Horizon documentary screened in August 2012 [7]. The ‘Fast Diet’ [8] or ‘5-2 Diet’ has since attracted much attention among people trying to lose weight, and it remains highly popular. The simple principle of this approach is caloric restriction (500 kcal for women and 600 kcal for men) on two non-consecutive days each week [8].

IER is not a new concept. The first RCT of IER was published some 30 years ago [9]. However, the previous versions of IER required fasting on every other day or on consecutive days, and they also required caloric restrictions on non-fasting days. Unsurprisingly, they did not have a wide appeal, but several studies have been published.

Narrative reviews of IER [13–15] draw heavily on animal data and highlight the paucity of human trials, but we identified several studies evaluating earlier versions of IER [9–12, 16–23]. Typically, participants were asked to restrict energy by 75% every other day or on two consecutive days per week, sometimes after a period of very-low calorie diet, and they were also asked to use prescriptive diets on non-fasting days. IER was as effective as continuous energy restriction and had better effects on e.g. insulin sensitivity and lipid profiles. This provides encouraging proof-of-principle evidence, but the generalizability of the results and practicability of these interventions is limited. The studies were small and participants were carefully selected. In some studies they had to pass a pre-test of 2-day energy restriction and typically over 50% of eligible participants declined participation or were unable to cope with the pre-test fasting.

The main advantage of the 5-2 diet responsible for its popularity seems to be its simplicity, the recommendation that fasting takes place on separate days (‘going hungry’ for two consecutive days seems too difficult for most people), and the removal of food restrictions on non-fasting days. Unlike most other approaches to weight loss, the 5-2 diet does not require relentless self-control, but allows people to stop worrying about food intake on 5 days a week. Numerous internet fora provide extensive reports of success and document considerable public enthusiasm for the 5-2 diet. Compared to previous approaches to intermittent fasting, this less restrictive regime may have a weaker effect, but this is likely to be compensated for by better adherence and sustainability of the intervention. The approach is easy to disseminate and given its attractiveness to dieters, if it is effective, it could have a considerable potential for wide-spread use and for public health benefit.

No trials have evaluated this version of IER so far and there is a need to evaluate its short-term effects when delivered in the formats amenable for wide-spread use and with populations that will most benefit from such options.

**Risks and benefits**

The 5-2 diet generates a degree of hunger and discomfort on the fasting days, especially initially, but apart from this it conveys no known risks. The potential benefits include weight loss [15], improvements in insulin levels and insulin sensitivity [24, 25], and possible improvements in circulating cholesterol, triglycerides, and blood pressure [26, 27].

**Rationale for the current study**

Given the current popularity of the 5-2 diet, and the lack of data on its effectiveness, information is needed on whether it generates short-term weight loss and what is the most effective mode of its delivery, particularly in the community settings where standard approaches have low penetration and low efficacy.

A number of clients at our weight management programmes have reported their experience with the 5-2 diet and we have also piloted its use at our clinics. This identified some barriers such as finding suitable foods and planning meals for the fasting days, but the main hurdle to implementing the 5-2 diet is the hunger and discomfort on the fasting days. Our experience confirms that people who stick with the programme typically learn to tolerate the fasting days well, especially once they see the positive results. We now believe that although the diet in its usual self-help format can help some people, it is likely to be more effective if group support is included to assist adherence over the first few weeks. After this initial period, the diet should be much easier to maintain without further external support.

We propose to investigate the initial effects of the 5-2 diet delivered in two different formats (self-help and with group support), both of which are amenable for wide-spread use.

### TRIAL OBJECTIVES

To evaluate the short-term weight loss achieved with the 5-2 diet combined with multi-session behavioural support compared to the 5-2 diet delivered in a self help format and standard advice on diet and physical activity.

**Primary Outcome**

Weight loss at six months

**Secondary Outcomes**

1. Changes in weight, blood pressure, dietary habits, exercise levels and proportion of participants losing at least 5% of their body weight, at 6 weeks, 6 and 12 months and the self-reported change in weight at 3 months
2. Adherence to the three interventions, determinants of adherence, and barriers and facilitators to adherence.

**Trial Design**

Randomised controlled trial (RCT)

### METHODOLOGY

**Inclusion Criteria**

- Age 18 years and older
- BMI≥30kg/m2, or BMI≥28kg/m2 with comorbidities

**Exclusion criteria**

- Women who are pregnant, breastfeeding or planning to conceive in the next 6 months
- History of eating disorders
- Currently involved in another research project
- Currently using 5:2 diet
- Non English speakers
- Unavailable for 6 month follow-up
- BMI>45kg/m2
- Lost more than 5% of their body weight in the last 6 months
- Taking medication prescribed by a psychiatrist (these medications can affect weight and psychiatric illness makes adherence to long-term programs difficult)
- Diabetics who require insulin
- Participant has undergone any form of bariatric surgery

We are not excluding any other co-morbidities to ensure the study addresses NHS needs and the results are generalizable.

**Criteria for premature withdrawal**

Participants will be followed up at 12 months unless they explicitly want no further contact.

**Study Design / Plan – Study Visits**

**Study Scheme Diagram**

| **Recruitment**  Potential participants will contact the study team via phone/email after seeing study advertisements in local newspapers and on the internet. Staff will provide information about the study and if the potential participant is interested, they will be screened. If eligible, they will receive an appointment for the baseline visit and sent the Participant Information Sheet (PIS) and booking confirmation. The phone call will take up to 20 minutes. | | | | | | | |
| --- | --- | --- | --- | --- | --- | --- | --- |
|  |  | | |  | |  |  |
| **Baseline visit**  Participants will receive information about the study and provide written informed consent; baseline data will be obtained including weight, height, blood pressure and demographic details; eating and physical activity questionnaires will be completed.  Participants will be randomised to 5-2 Behavioural support, 5-2 self-help, or standard advice arms. | | | | | | | |
|  | |  |  | |  | |  |
| **5-2 self-help (5-2 SH)**  **(N=100)**  20 minute session on the 5-2 plan, a written guide on how to use it with recommendations for internet and other resources and a leaflet listing local resources for exercise. | |  | **5-2 plus group support (5-2 GS) (N=100)**  Participants receive the same materials as in the 5-2 self-help condition and attend 6 weekly group support sessions. | |  | **Standard advice self help (SH) (N=100)**  20-minute session  on healthy eating and physical activity and the British Heart Foundation guides Facts Not Fads and Get Active, Stay Active plus the NHS Change  4 Life series of booklets and a leaflet listing local resources for exercise. | |
|  | |  |  | |  |  | |
| **6 week follow up**  Measurement of weight and blood pressure; recording of any concomitant weight management treatments; adherence to and ratings of 5-2 diet | |  | **6 week follow up**  Measurement of weight and blood pressure; recording of any concomitant weight management treatments; adherence to and ratings of 5-2 diet | |  | **6 week follow up**  Measurement of weight and blood pressure; recording of any concomitant weight management treatments; adherence to and ratings of advice components | |
|  | |  |  | |  |  | |
| **3 month follow up phone call**  Self-report weight; adherence to and ratings of 5-2 diet; recording of any concomitant weight management treatments | |  | **3 month follow up phone call**  Self-report weight; adherence to and ratings of 5-2 diet; recording of any concomitant weight management treatments | |  | **3 month follow up phone call**  Self-report weight; adherence to and ratings of the advice components; recording of any concomitant weight management treatments | |

| **6 month follow up**  Measurement of weight and blood pressure; adherence to and ratings of 5-2 diet; recording of any concomitant weight management treatments; change in eating habits; change in exercise levels (IPAQ) |  | **6 month follow up**  Measurement of weight and blood pressure; adherence to and ratings of 5-2 diet; recording of any concomitant weight management treatments; change in eating habits; change in exercise levels (IPAQ) |  | **6 month follow up**  Measurement of weight and blood pressure; adherence to and ratings of the advice components; recording of any concomitant weight management treatments; change in eating habits; change in exercise levels (IPAQ) |
| --- | --- | --- | --- | --- |

Pending their consent to continue in the study, participants will be followed up at 12-months (see the above 6 month follow-up for details of assessment).

### STUDY PROCEDURES

**Recruitment**

Participants would be recruited via the following methods; advertising in newspapers including the Evening Standard, Metro and local papers; adverts on social media and on internet fora and through GP practices; online bulletins; leaflets and posters in community venues; leaflets via mail drops; texting previous weight clinic participants.

**Informed Consent**

Participants will receive a PIS with details of the study and will have at least 24 hours before signing the informed consent form (ICF).

**Screening**

Participants who meet the inclusion criteria over the phone will attend the baseline session. They will provide written informed consent, provide baseline measures and get randomised to one of the three study arms.

**Randomisation**

Randomisation would be computer-generated by the study statistician, using envelopes to reveal the randomisation allocation.

**Schedule of Assessment**

| **Time** | **Baseline** | **6 weeks** | **3 months** | **6 and 12 months** |
| --- | --- | --- | --- | --- |
| Demographics | X |  |  |  |
| Weight loss history | X |  |  |  |
| Weight | X | X | X (self-report) | X |
| Height | X |  |  |  |
| Blood pressure | X | X |  | X |
| Co-morbidities | X | X | - | X |
| Concurrent medications | X | X | - | X |
| International Physical Activity Questionnaire (IPAQ) | X | X | - | X |
| Diet Quality Questionnaire | X | X | - | X |
| Use of non-trial slimming methods | X | X | X | X |
| Feedback on treatment |  | X | - | X |
| Adherence to 5-2/advice |  | X* | X* | X* |
| Ratings of 5-2/advice |  | X** | - | X** |

**End of Study Definition**

The last participant completes the 12-month follow-up.

**Participant withdrawal**

Participants will be able to withdraw from the study at any time. Data already collected will be used in the final analysis, provided the participant consents to their data collected to date to be used.

**Study arm treatments**

**5-2 self-help (5-2 SH) arm** would receive a 20-minute session on the 5-2 plan and a written guide on how to use it with recommendations for internet resources along with a leaflet listing local resources for exercise. Participants will be encouraged to purchase and use pedometers to increase their exercise levels and to assess their weight weekly. In both 5-2 arms, participants will be asked to reduce their energy intake on two non-consecutive days per week to 500 calories for women and 600 calories for men. Participants will be seen by Research Health Psychologists.

**5-2 plus group support (5-2 GS) arm** would receive a brief explanation of the 5-2 plan and will be booked for six weekly group support sessions. Participants would also receive a leaflet listing local resources for exercise and will be encouraged to purchase and use pedometers to increase their exercise levels and to assess their weight weekly. The sessions will focus on helping clients to adhere to 5-2, share coping and fasting strategies and maintain motivation. Each session would last for approximately one hour and groups will comprise of 10-20 participants. Research Health Psychologists will run the groups.

**Standard advice self-help (SH) arm** would receive a 20-minutes session with an advisor focusing on healthy eating and physical activity and instructions on using the ‘Facts not Fads’ and the ‘Get Active, Stay Active’ British Heart Foundation self-help guides, supplemented by the NHS Change 4 Life series of booklets and a leaflet listing local resources for exercise. Participants will be encouraged to use pedometers to increase their exercise levels and to assess their weight weekly. Participants will be seen by Research Health Psychologists.

All sessions will be held at the Health and Lifestyle Research Unit, [name].

All participants will receive £20 for their travel and time at the 6 week and 6 and 12 month follow-up visits.

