### STATISTICAL CONSIDERATIONS

**Primary Endpoint Efficacy Analysis**

Change in weight from baseline at 6 months after enrolment into the study.

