**Statistical Analysis**

Analyses will be undertaken after the last participant has completed the 6-month follow-up. ITT analysis will be conducted as the primary outcome, with participants lost to follow-up included as achieving no weight loss. 'Last-weight-carried-forward' imputation and 'completers only' analysis limited to participants who provide follow-up data are reported as sole outcomes in many weight loss trials. To allow comparison across studies, we will conduct such analyses as well.

Weight change will be analysed by analysis of variance (ANOVA) with comparisons between all pairs of the three groups.

We shall also examine the effect of age, socioeconomic grouping, BMI at baseline and gender on weight loss and include any univariately significant variables in an analysis of covariance (ANCOVA) of weight change alongside study arm allocation. We shall assess, via interaction, the moderator effects of these variables on weight loss.

We will also calculate the proportion of randomised participants who achieved at least 5% weight loss and odds ratios for percentage weight change will be analysed via logistic regression.

Further to this, we will report group sessions attended in the 5-2 BS arm, and adherence to 5-2 in both 5-2 arms, together with 5-2 ratings; and report adherence to and evaluation of elements of the advice provided in SH arm, concerning changes in diet and exercise levels. IPAQ and FFDBQ scores in the three study arms will be compared using ANOVA.

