**Sample Size**

In this early phase primary research, we opted for a pragmatic sample size

achievable economically and quickly but large enough to provide reasonable confidence intervals on the key estimates. We aim to randomise 100 participants in each study arm.

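### The group-support arm is treated in roughly 5-10 groups but analysed as 100 independent participants, so both comparisons with that arm will look too precise if outcomes correlate within groups

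*Protocol*

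**What the plan says.** Participants are randomised individually: under Screening they "provide baseline measures and get randomised to one of the three study arms". Under Sample Size the Protocol states: "We aim to randomise 100 participants in each study arm".

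Only one arm is treated in groups. Under Study arm treatments, 5-2 GS participants "will be booked for six weekly group support sessions", and "Each session would last for approximately one hour and groups will comprise of 10-20 participants". Interaction between members is part of the treatment: "The sessions will focus on helping clients to adhere to 5-2, share coping and fasting strategies and maintain motivation". The 5-2 self-help and standard advice arms receive a single 20-minute session and written materials.

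The primary endpoint is "Change in weight from baseline at 6 months after enrolment into the study". Under Statistical Analysis: "Weight change will be analysed by analysis of variance (ANOVA) with comparisons between all pairs of the three groups". A further model is to "include any univariately significant variables in an analysis of covariance (ANCOVA) of weight change alongside study arm allocation", and the 5% weight-loss outcome is analysed by logistic regression. Nothing in the Protocol mentions support group as a factor, clustering, an intraclass correlation, a random effect or robust standard errors. The Sample Size section makes no allowance for clustering.

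**The concern.** This is a partially nested design: individual randomisation, with clustering created by treatment in one arm only. Members of one support group share sessions, peers and group dynamics for six weeks. The Protocol's rationale is that this support helps people adhere to the diet. If it works in that way, members of one group may do better or worse together, and 100 participants then carry less information than 100 independent ones.

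ANOVA, ANCOVA on participant-level covariates and ordinary logistic regression all assume independence. The stated objective is to compare GS with 5-2 self-help and with standard advice, so the clustered arm is in both comparisons of interest. The Sample Size section justifies 100 per arm only by the width of the confidence intervals it should deliver. An understated width therefore bears on the one design criterion the Protocol gives.

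**Working it through.** The Protocol states no power, effect size, SD or alpha, so there is no figure of its own to reproduce.

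**Inputs from the Protocol**
- 100 participants per arm (Sample Size).
- Group size m = 10-20, GS arm only (Study arm treatments). The number of groups is 100/20 = 5 to 100/10 = 10.

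**Assumptions, not in the Protocol**
- Two-sided 5% level for each comparison.
- ICC within support groups from 0 to 0.10.
- Equal total variance in the arms, with results in SD units.

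**Step 1: what the ANOVA assumes.** SE = SD × √(2/100), so the 95% half-width is 1.96 × √0.02 = 0.277 SD.

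**Step 2: clustering in the GS arm only.** The variance of the GS mean is multiplied by DE = 1 + (m − 1) × ICC, and the comparator arm is unchanged. Hence:
- true SE / ANOVA SE = √((1 + DE)/2)
- actual type I error = 2 × (1 − Φ(1.96 / ratio))
- effective n in GS = 100 / DE

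Worked case, m = 15 and ICC = 0.05: DE = 1 + 14 × 0.05 = 1.70; effective n = 100/1.70 = 59; ratio = √(2.70/2) = 1.162; type I error = 2 × (1 − Φ(1.96/1.162)) = 9.2%.

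| m | ICC | DE | Effective n (GS) | SE ratio | Type I error | Normal-theory half-width (SD) |
|---|---|---|---|---|---|---|
| any | 0 | 1.00 | 100 | 1.00 | 5.0% | 0.277 |
| 10 | 0.01 | 1.09 | 92 | 1.02 | 5.5% | 0.283 |
| 20 | 0.01 | 1.19 | 84 | 1.05 | 6.1% | 0.290 |
| 10 | 0.05 | 1.45 | 69 | 1.11 | 7.7% | 0.307 |
| 15 | 0.05 | 1.70 | 59 | 1.16 | 9.2% | 0.322 |
| 20 | 0.05 | 1.95 | 51 | 1.21 | 10.7% | 0.337 |
| 10 | 0.10 | 1.90 | 53 | 1.20 | 10.4% | 0.334 |
| 20 | 0.10 | 2.90 | 34 | 1.40 | 16.0% | 0.387 |

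**Step 3: simulation check.** I simulated 20,000 trials per setting with three arms of 100, pooled-variance pairwise tests on 297 degrees of freedom, and clustering in GS only.
- At ICC 0.05 the two GS comparisons rejected in about 7.6% (m = 10), 9.2% (m = 15) and 10.5% (m = 20) of trials.
- At ICC 0.10 and m = 20 they rejected in about 16%.
- 5-2 self-help versus standard advice stayed at 4.7-5.3% in every setting.
- The overall F test was also inflated, at 7.4-10.3% for ICC 0.05.

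**Step 4: interval width under a correct analysis.** With few groups, the critical value rises as well as the standard error. The approximate Satterthwaite formula, with k = 100/m groups, is df = (DE + 1)² / (DE²/(k − 1) + 1/99).
- m = 15, ICC 0.05: df = 2.70² / (1.70²/5.67 + 1/99) ≈ 14, t ≈ 2.14. Width relative to independence is 1.162 × 2.14/1.96 ≈ 1.27.
- m = 20, ICC 0.10: df = 3.90² / (2.90²/4 + 1/99) ≈ 7.2, t ≈ 2.35. Width relative to independence is 1.396 × 2.35/1.96 ≈ 1.68.

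**The case against.** A reader might infer that the planned standard errors are certainly too small and that the false-positive rate certainly exceeds 5%. The documents do not support that. They give no ICC and no alpha. At ICC 0 the ANOVA is valid, and at 0.01 the inflation is slight (5.5-6.1%). Because randomisation is individual and groups form afterwards, support that affects nobody creates no treatment-induced correlation, and the ANOVA keeps roughly its nominal level. Inflation arises under the weaker null of a zero average effect with real differences between groups. All of this stands, and the conclusion is conditional for that reason.

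There are also reasons to expect a modest ICC. Group contact lasts six weeks, while the endpoint is at six months. Research Health Psychologists see participants in all three arms, so shared staff is not peculiar to GS. Partial attendance, mixing between groups and counting dropouts as no weight loss could dilute the correlation. These points bear on the size of the effect; they do not show that the ICC is zero.

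It can also be said that model detail belongs in a SAP that is not shown. Random effects and degrees of freedom often do. But the Protocol does not leave the method open: it names ANOVA, ANCOVA and logistic regression, with study arm as the only design factor.

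Finally, the Protocol presents the trial as early-phase work with a pragmatic size and claims no power. That argues against treating this as a fatal flaw. It does not excuse intervals that may be too narrow when interval width is the stated reason for the sample size.

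**Conclusion.** The concern holds conditionally. The Protocol describes a partially nested design and fixes an analysis that ignores the nesting. If the ICC is above zero, which is plausible because shared strategies and motivation are what the sessions are meant to deliver, the confidence intervals for GS versus 5-2 self-help and GS versus standard advice are too narrow.

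Over an assumed ICC of 0.01-0.10 and the stated group sizes, the ANOVA standard error is too small by a factor of 1.02 to 1.40. Type I error for a zero average effect runs from about 5.5% to 16%. The upper figure pairs the largest group size with the largest assumed ICC. The estimated differences in weight change are not biased, and 5-2 self-help versus standard advice is unaffected. This should be fixed; it does not invalidate the trial.

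**What to change.** 1. Record a support-group identifier for every GS participant. Neither the CRF list nor the analysis section names one, and without it the correlation cannot be modelled later. The Protocol does not say whether groups are closed or rolling, so define the identifier as the group first allocated if membership changes.
2. In Statistical Analysis, specify a partially nested model for weight change: a random support-group effect in the GS arm only, arm-specific residual variance, and Satterthwaite or Kenward-Roger degrees of freedom. Use the corresponding random group effect in the model for the 5% weight-loss outcome.
3. Report the estimated ICC, and keep the planned ANOVA as a sensitivity analysis.

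The cost is one data field and a few sentences; treatment, visits and sample size do not change. The statistical cost is real. With 5-10 groups the ICC will be poorly estimated, and the two GS intervals may be noticeably wider than under independence: about 27% at ICC 0.05 with groups of 15, and up to about 68% at ICC 0.10 with groups of 20.
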